### Participants

#### Eligibility criteria

Male individuals of legal age diagnosed with locally advanced or metastatic prostate cancer and undergoing androgen deprivation therapy (ADT) are eligible for inclusion in this randomized controlled trial. The primary objective was to assess the impact of a structured physical exercise intervention on physical function, cancer-related fatigue, and quality of life in this patient population. Participants are randomly allocated to one of two groups: those in the intervention arm received supervised exercise in accordance with the SPoRT-PCa-ADT Program, while those in the control arm are provided with a home-based exercise regimen following an initial evaluation, supported by weekly telephone follow-ups.

The inclusion and exclusion criteria are presented in the Table 1, following the recommendations of previous randomized controlled trials to target an clinically homogeneous population, maximizing potential benefits and be consistent with exercise guidelines for cancer patients [8, 22].

**Table 1 Tab1:** Inclusion and exclusion criteria

Inclusion criteria	Male participants aged 18–80 years Diagnosis of locally advanced or metastatic prostate cancer Currently receiving androgen deprivation therapy (ADT) Treatment at Urology and oncology departments within the University Clinical Hospital “Virgen de la Arrixaca” healthcare network Legal capacity and signed informed consent Ability to attend supervised sessions or perform home-based exercises safely Physician clearance for exercise participation
*Exclusion criteria*	Unwillingness to participate in the study Inability to complete adequate follow-up Uncontrolled or symptomatic metastatic bone disease Physical disabilities that would prevent participants from safely completing the protocol Severe cardiovascular disease or contraindications to exercise determined by assessment Participation in structured resistance training within the previous 6 months Cognitive impairment limiting ability to follow exercise instructions Uncontrolled hypertension (> 160/100 mmHg) Active treatment for other primary cancers

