#### Sample size

Sample size calculations are performed using G*Power 3.1.9.7 software [23]. For the primary analysis examining the time × treatment interaction effect, an F-test for ANOVA: repeated measures, within-between interaction is selected. Parameters are set as follows: effect size f = 0.25 (converted from Cohen’s d = 0.5), α error probability = 0.05, power (1-β error probability) = 0.95, number of groups = 2, number of measurements = 3 (baseline, midpoint, post-intervention), correlation among repeated measures = 0.5 (estimated from previous resistance training studies in cancer populations), and nonsphericity correction ε = 1. The moderate effect size (Cohen’s d = 0.5) is selected based on previous research demonstrating moderate to large effects of resistance training interventions on muscle strength and functional outcomes in ADT patients [24, 25]. This analysis determines that 44 participants (22 per group) provide adequate statistical power to detect the hypothesized interaction effect for the primary outcome measures. Accounting for an anticipated 15% dropout rate, based on previous reports from supervised exercise interventions in cancer survivors, 52 participants are targeted for recruitment (26 per group randomized to either the supervised velocity-based training program or the home-based control intervention).

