### Statistical analyses

Statistical analyses will be performed using JAMOVI (version 2.5, The JAMOVI Project, Sydney, Australia). Descriptive statistics will be calculated for all variables, with data presented as means and standard deviations for continuous variables and frequencies and percentages for categorical variables. Graphical representations will be generated using GraphPad Prism (version 10, GraphPad Software Inc., San Diego, CA, USA).

The primary analysis will include all participants who completed both baseline and post-intervention assessments in their respective groups. Additional sensitivity analyses will be conducted using intention-to-treat principles, with missing data handled using multiple imputation by chained equations (MICE) with predictive mean matching for continuous variables. For all outcome measures, analysis of covariance (ANCOVA) will be used to compare post-intervention values between groups while adjusting for baseline values and stratification variables (age group and ADT duration).

Bonferroni post-hoc corrections will be applied for multiple comparisons across outcome measures. Effect sizes will be calculated using Cohen’s d for between-group differences and partial eta-squared for ANCOVA models, with values of 0.2, 0.5, and 0.8 considered small, medium, and large effects for Cohen’s d, respectively [45]. For all analyses, *p* < 0.05 will be considered statistically significant. Per-protocol analyses will be conducted as sensitivity analyses, including only participants with ≥ 85% adherence. Exploratory subgroup analyses will examine potential effect modification by baseline characteristics including age, ADT duration, and baseline functional status. Correlation analyses will examine relationships between changes in objective physical performance measures and patient-reported outcomes within each group.

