### Dissemination policy

The results of the SPoRT-Pca-ADT trial will be disseminated regardless of the direction or magnitude of findings. Primary outcomes will be submitted for publication in peer-reviewed journals in the fields of exercise oncology and urology, with secondary outcomes reported in subsequent publications. Findings will also be presented at relevant national and international scientific conferences. A summary of results will be communicated to participants upon study completion and shared with the prostate cancer patient community through the Never Surrender Foundation and the referring clinical teams at the Urology Department of the University Clinical Hospital ‘Virgen de la Arrixaca’. Summary results will be posted on ClinicalTrials.gov (NCT07064811) within 12 months of trial completion.

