The implementation model of the SPoRT-PCa-ADT Program (collaboration between a specialized sports center and a hospital-based urology department) represents a hybrid approach between clinical and community settings. This differs from both hospital-based programs like the BEAUTY program [48] and purely community-based approaches like LIVESTRONG at the YMCA [46], or FitSTEPS for Life [54]. Our approach most closely resembles the model described by Cormie et al. [21, 55] which utilized exercise physiologists in community settings with medical oversight. However, while Cormie et al.‘s program employed general exercise physiologists, the SPoRT-PCa-ADT Program specifically utilized sports scientists with specialized training in velocity-based methodologies, reflecting the technical demands of the intervention approach. The supervised nature of our program (twice weekly with monitoring of specific performance parameters) contrasts with more self-directed approaches such as the home-based components described in the PERFECT study [47] and Hojan et al. [56]. While supervised exercise is generally associated with better outcomes in cancer patients [57, 58], the resource requirements of such approaches must be considered in the context of scalability and implementation.

The assessment methods used in the SPoRT-PCa-ADT Program include several measures common to exercise oncology research (400-meter walk test, chair rise test, anthropometry) but also incorporate specialized assessments not typically included in previous studies. The use of movement velocity measurements (mean propulsive velocity) and detailed force-time analysis during isometric testing provides more comprehensive assessment of neuromuscular function than the strength and functional assessments typically employed in previous research. For example, while the PERFECT study [47] utilizes VO2peak and muscle strength as primary physical fitness outcomes, our protocol’s inclusion of velocity-based metrics and rate of force development measures offers potential insights into neuromuscular adaptations that may be particularly relevant to functional performance in daily activities. This expanded assessment approach aligns with recommendations from Stout et al. [18] regarding comprehensive evaluation of exercise effects in cancer patients.

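### No primary outcome variable is named and the Bonferroni family is undefined, while the 95% power is computed at an unadjusted alpha of 0.05

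*Protocol article*

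**What the plan says.** All references are to the Protocol article.

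- **Objective** (Eligibility criteria): "The primary objective was to assess the impact of a structured physical exercise intervention on physical function, cancer-related fatigue, and quality of life". These are three domains, and no variable is attached to any of them.
- **Sample size**: 44 participants are said to "provide adequate statistical power to detect the hypothesized interaction effect for the primary outcome measures". The inputs are "α error probability = 0.05, power (1-β error probability) = 0.95", effect size f = 0.25, three measurements and a correlation of 0.5. The primary measures are plural and unnamed.
- **Statistical analyses**: ANCOVA of post-intervention values is planned for every outcome, adjusted for baseline and the two stratification factors. Then: "Bonferroni post-hoc corrections will be applied for multiple comparisons across outcome measures". Later in the same paragraph, p < 0.05 "will be considered statistically significant" for all analyses.
- **Dissemination policy**: "Primary outcomes will be submitted for publication in peer-reviewed journals", "with secondary outcomes reported in subsequent publications". This relies on a primary/secondary split that the article does not make.

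**The concern.** The sample size, the analysis and the publication plan all depend on knowing which outcome is primary, and the article does not say. Physical function alone could mean the progressive loading test, jump height, maximum isometric force or any of four rate-of-force-development measures.

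Bonferroni across outcome measures means nothing until the number of tests is fixed, because that number sets the alpha for each test. Whatever number above one is chosen, the alpha applied to an outcome will be smaller than the 0.05 used to justify 44 participants. If the family is left open until unblinded data are seen, both the outcome presented as primary and the divisor could be chosen with knowledge of the results, and a confirmatory claim would then be hard to defend.

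**Working it through.** **1. Reproduce the stated figure.** Inputs from Sample size: f = 0.25, N = 44, k = 2 groups, m = 3 measurements, ρ = 0.5, ε = 1, α = 0.05.

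- λ = f² × N × m / (1 − ρ) = 0.0625 × 44 × 3 / 0.5 = 16.5
- df1 = (k − 1)(m − 1) = 2; df2 = (N − k)(m − 1) = 84
- Power from the noncentral F distribution: 0.956. With N = 42 it is 0.946.

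So 44 is right for these inputs. Dropout: 44 / 0.85 = 51.8, rounded up to 52, which also agrees.

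**2. Choose illustrative family sizes.** The article gives none, so these are assumptions.

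- 3: one outcome per domain of the primary objective.
- 13: the physical and patient-reported measures. Loading test 1, jump 1, isometric 5 (maximum force, RFDmax and three interval RFDs), questionnaires 6 (BFI, FACT-P, HADS anxiety, HADS depression, IPSS, PSQI). 1 + 1 + 5 + 6 = 13.
- 22: the 13 plus 3 anthropometric measures (weight, body composition, BMI) and 6 blood markers. 13 + 3 + 6 = 22.

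Bonferroni alphas: 0.05/3 = 0.0167, 0.05/13 = 0.0038, 0.05/22 = 0.0023.

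**3. Apply them to the article's own power model** (λ = 16.5, df 2 and 84).

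| Tests | Alpha per test | Power |
|---|---|---|
| 1 | 0.05 | 0.956 |
| 3 | 0.0167 | 0.895 |
| 13 | 0.0038 | 0.768 |
| 22 | 0.0023 | 0.714 |

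(The 3-test value is 0.8947 before rounding, hence about 89%.)

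**4. Apply them to the planned ANCOVA.** Two-sided noncentral t with n = 22 per arm and d = 0.5. The noncentrality is d × √(n/2) / √(1 − r²), with df = 2n − 5 = 39 (two groups, baseline and two stratification covariates). The baseline-to-post correlation r is an assumption. The article gives 0.5 as the correlation among repeated measures, so r = 0.5 is the natural value, and 0 and 0.7 show the range. At r = 0.5 the noncentrality is 0.5 × √11 / √0.75 = 1.915.

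| Tests | r = 0 | r = 0.5 | r = 0.7 |
|---|---|---|---|
| 1 | 37% | 46% | 62% |
| 3 | 21% | 29% | 44% |
| 13 | 9% | 14% | 24% |
| 22 | 7% | 11% | 19% |

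At d = 0.8 and r = 0.5 the column reads 85%, 71%, 50% and 43%.

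**5. Separate the two causes.** At r = 0.5, the fall from 96% to 46% happens with one outcome at 0.05. It arises because N was derived for a three-timepoint interaction test and the analysis compares post-intervention values. Multiplicity accounts for the further fall from 46% to 29%, 14% or 11%.

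**6. Participants per arm for 80% power** (ANCOVA, d = 0.5, r = 0.5): 49 for one test at 0.05, and 65 for three Bonferroni tests.

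**The case against.** **The two significance sentences contradict each other.** A reader might infer this, but the text does not support it. Bonferroni-adjusted p-values are routinely compared with 0.05, and on that reading both sentences hold. Family-wise error rates of 14% for 3 independent tests (1 − 0.95³) or 68% for 22 (1 − 0.95²²) would arise only if the stated correction were ignored, and the article does not plan that.

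**Bonferroni leaves the trial with almost no power.** This is also tempting and too strong. On the article's own model, 71% to 89% remains for 3 to 22 tests. The 11% figure needs the ANCOVA, d = 0.5, r = 0.5 and a family of 22. That family takes in the anthropometric and blood measures listed under Additional clinical measures, and nothing says the correction reaches that far. The article cites moderate to large effects, and d = 0.8 gives much higher power. Most of the loss under ANCOVA is the separate model mismatch.

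**The full protocol, analysis plan or registry entry may name the primary outcome.** They may, and the article does not show that the choice would be made after seeing the data. It also requires ethics approval and a registry update for changes to outcomes or analyses. What stands is that the article itself pairs an unadjusted alpha with a correction across outcomes, and those two statements need aligning wherever the primary outcome is recorded.

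**Several primary outcomes are legitimate.** Agreed, provided that the set and the error control are stated.

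The Discussion also lists among the assessments "400-meter walk test, chair rise test, anthropometry"; the walk and chair rise tests are not described in the Methods. That is a separate reporting inconsistency and carries no weight here.

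**Conclusion.** The point holds in a limited form. The article designates no primary variable, leaves the Bonferroni family open and states power at an alpha that its own multiplicity rule would not allow once more than one outcome is in the family. On its own model the overstatement is modest for three tests (96% to about 89%) and material for 13 or 22 (77% and 71%). For the ANCOVA that will be run, power at d = 0.5 is 29% for three tests and 11% for 22 at r = 0.5, or 44% and 19% at r = 0.7, starting from 46% and 62% for a single test.

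The family sizes and the use of r as the baseline-to-post correlation are assumptions. The mismatch between stated power and stated correction depends on neither. Naming a single primary outcome would settle the error rate but would not restore 95% power.

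**What to change.** Amend Sample size and Statistical analyses together, before any unblinded data are seen:

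1. Either name one primary variable at week 24, tested at two-sided 0.05, or name a small co-primary set (for example one variable for each domain of the primary objective) with the number of tests stated and a Holm or Bonferroni procedure.
2. Label all other outcomes secondary or exploratory, reported with estimates and 95% confidence intervals.
3. Replace the blanket Bonferroni sentence with one that states the family, the number of tests and whether adjusted p-values are compared with 0.05.
4. Restate power for the planned ANCOVA at the alpha actually used, giving the assumed baseline-to-post correlation.

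Cost: a protocol and registry amendment, by the route the Design section already provides; a less favourable stated power; and loss of the option to claim success on any of several outcomes.

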##### Maximum isometric contraction test

Maximum isometric force (MIF) and maximum rate of force development (RFDmax) are measured during a maximum voluntary isometric contraction (MVIC) test in the squat (SQ) exercise with participants standing and knees flexed at 90° (180° = full extension). This test is performed on a quadriceps extension machine. Participants are instructed to push against the force platform as quickly and forcefully as possible following the “ready, set, go!” signal during two 5-second trials separated by 1-minute rests. External forces are recorded at a sampling rate of 1000 Hz and processed using specific software (Chronojump Boscosystem^®^, Barcelona, Spain). RFDmax is calculated as the maximum slope in the time-force curve over 20 ms intervals. Additionally, the average tangential slope of the time-force curve is obtained at different time intervals (50, 100, and 150 ms from the onset of force production, RFD0-50, RFD0-100, and RFD0-150, respectively) was calculated. The average value of each variable from the two attempts is recorded.

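### Bonferroni across outcomes is valid, but Holm's step-down gives the same family-wise protection, never rejects fewer outcomes, and would be a cheap improvement

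*Protocol article*

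**What the plan says.** The Statistical analyses section applies one model throughout: "For all outcome measures, analysis of covariance (ANCOVA) will be used to compare post-intervention values between groups", with adjustment for baseline and the two stratification factors. For multiplicity it states: "Bonferroni post-hoc corrections will be applied for multiple comparisons across outcome measures". The threshold is p < 0.05 for all analyses. The effect measures named are Cohen's d "for between-group differences and partial eta-squared for ANCOVA models"; confidence intervals are not mentioned.

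The article does not give the number of outcomes in the family. Two places show that success is meant to be judged on more than one outcome. The Eligibility criteria section gives a primary objective covering physical function, cancer-related fatigue and quality of life. The Sample size section says that 44 participants "provide adequate statistical power to detect the hypothesized interaction effect for the primary outcome measures". That calculation uses "effect size f = 0.25" and "α error probability = 0.05".

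**The concern.** Bonferroni holds every outcome to 0.05/m, however many of the other outcomes have already been rejected. Holm relaxes the threshold after each rejection and needs no further assumption.

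The programme is built around the squat, so strength and velocity measures may well respond first. Under Bonferroni, clear success there does nothing for the threshold applied to fatigue or quality of life. Under Holm it does. With about 22 analysed men per arm, power per outcome is low after any adjustment, so an improvement that keeps the same error guarantee is worth having. At stake is some avoidable loss of power on the second and later outcomes. Bias and excess false positives are not in question.

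**Working it through.** **Inputs from the Sample size section.** 22 evaluable per arm; f = 0.25 (d = 0.5); correlation among repeated measures 0.5; three measurements; alpha 0.05; power 0.95; 15% dropout.

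**Assumptions, not in the article.** Two-sided tests. The repeated-measures correlation of 0.5 is used as the baseline-to-post correlation. The family size is m = 3 to 15, with a worked case of m = 14 (7 physical measures, 7 questionnaire scores). In the worked case, residual correlations are 0.6 among physical outcomes, 0.4 among questionnaire scores and 0.15 between the two sets. d = 0.8 is tried as a larger effect, since the section cites moderate to large effects on strength and function.

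**1. The plan's own figure.** Noncentrality is f² × N × measurements / (1 − correlation). For N = 44 this is 0.0625 × 44 × 3 / 0.5 = 16.5 on 2 and 84 degrees of freedom, giving power 0.956. For N = 42 it is 15.75, giving 0.946. So 44 reproduces, and 44 / 0.85 = 51.8 rounds up to 52. Neither figure depends on the multiplicity method, because alpha is not divided.

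**2. The two rules.** Order the p-values from smallest to largest.
- Bonferroni rejects each outcome with p ≤ 0.05/m.
- Holm rejects the i-th smallest if p(j) ≤ 0.05/(m − j + 1) for every j up to i.

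Three facts follow.
- *Never fewer rejections.* Every Holm threshold is at least 0.05/m, so any p-value passing Bonferroni, and all those below it, also pass Holm.
- *Same error control.* With m0 true nulls, the smallest true-null p-value stands at step m − m0 + 1 or earlier, so its threshold is at most 0.05/m0. The chance that any of the m0 falls below that is at most m0 × 0.05/m0 = 0.05, whatever the dependence.
- *Same chance of a first rejection.* Both test the smallest p-value at 0.05/m.

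With m = 14 the Bonferroni threshold stays at 0.05/14 = 0.0036. If seven outcomes have been rejected, Holm's next threshold is 0.05/7 = 0.0071.

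**3. Bonferroni power per outcome at m = 14.** ANCOVA noncentrality is d × √(n/2) / √(1 − ρ²).
- d = 0.5: 0.5 × 3.317 / 0.866 = 1.915.
- d = 0.8: 3.064.
- With 39 degrees of freedom the critical t at 0.05/14 is 3.101. Power is 13.5% and 49.4%.

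**4. Holm against Bonferroni on the same simulated data, m = 14** (40,000 replicates per scenario; rounding and simulation error of up to about one point)

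| True effects | Bonferroni | Holm |
|---|---|---|
| d = 0.5, all 14 | 14% | 16% |
| d = 0.5, physical only | 13.6% | 14.8% |
| d = 0.5, questionnaires only | 13.5% | 14.4% |
| d = 0.8 physical and 0.5 questionnaire: questionnaires | 13% | 19% |
| same: physical | 50% | 56% |

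In the mixed-effect scenario Holm rejected more outcomes in 42% of trials. No Bonferroni rejection was lost in any scenario. With d = 0.8 on physical outcomes and none on questionnaires, family-wise error on the questionnaires was 2.1–2.3% under Bonferroni and 3.1–3.8% under Holm.

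**5. Other family sizes, all outcomes affected** (between-outcome correlation 0 or 0.5)

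| m | d = 0.5: Bonferroni → Holm | d = 0.8: Bonferroni → Holm |
|---|---|---|
| 3 | 29% → 33–35% | 71% → 79–81% |
| 5 | 23% → 26–28% | 64% → 75–77% |
| 10 | 16% → 18–20% | 54% → 67–68% |
| 15 | 13% → 14–16% | 48% → 61% |

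With about half the outcomes affected, the gain is 0 to about 1 point at d = 0.5 and 0 to 4 points at d = 0.8. Family-wise error in mixed scenarios was 0.021–0.033 (Bonferroni) and 0.027–0.045 (Holm). With no true effects it was 0.039–0.051 and identical for both.

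**The case against.** The case for leaving the text alone is fair in several respects.

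- *Bonferroni is valid, prespecified and conservative.* This stands. It contradicts no other section, and no stated figure changes.
- *Bonferroni has directly matching simultaneous intervals at level 1 − 0.05/m; Holm has no equally simple ones.* This stands as a cost. A reader might infer that the plan gives away power for nothing, but this property of Bonferroni rules that out. Since the article mentions no confidence intervals, the plan as shown does not use the advantage.
- *The gain is small at the planned effect.* This stands. Larger gains need strong effects on most outcomes.
- *Correlated outcomes.* Several measures come from the same isometric trials ("50, 100, and 150 ms from the onset of force production, RFD0-50, RFD0-100, and RFD0-150, respectively"), and a reader might take that as a reason for Holm. It is not. Holm's thresholds ignore correlation just as Bonferroni's do. Correlation would argue for a smaller family or a method that uses the dependence.
- *Holm needs every p-value before any claim is made, while the Dissemination policy puts secondary outcomes in later papers.* This is a practical constraint only. All outcomes are collected by the post-intervention visit, so the family can be analysed together whatever the order of publication.
- *The family size is not given.* Bonferroni needs it just as much, so this does not favour either method.

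**Conclusion.** The point holds as a recommended improvement. It does not show a mistake in the protocol. Holm's equal error control and its never rejecting fewer outcomes are mathematical facts and rest on none of the assumed inputs.

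The size of the gain does rest on them: the family size, the number of outcomes truly affected, the effect sizes and the correlations. The planned d = 0.5 with 14 outcomes gives about 1 to 2.5 points. About 6 points requires d = 0.8 on all physical and 0.5 on all questionnaire outcomes. The upper end of about 14 points (m = 10, all outcomes at d = 0.8) is the most favourable case examined.

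A reader might also infer that Holm would repair the trial's power. It would not. At d = 0.5 under the stated ANCOVA, power is about 46% with no adjustment, 29% at 0.05/3 and 16% at 0.05/10. Holm recovers only a few points of that loss. The sample size's use of an undivided alpha is a separate matter.

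**What to change.** In the Statistical analyses section, replace Bonferroni with Holm (step-down Bonferroni) for the same family of outcome measures, before outcome data are analysed. Report the Holm-adjusted p-value beside each adjusted between-group difference.

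The edit is a change of a word or two. It needs no extra participants and does not loosen the error control. There are two small costs. Any 95% confidence intervals would be unadjusted and should be labelled so; an interval may then exclude zero beside a Holm-adjusted p-value above 0.05. All p-values in the family must also be computed together before any of them is declared significant.
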